#### Tailoring

This was a standardized group targeted program, with no individual tailoring.

#### Adherence/Fidelity

To ensure the intervention is conveyed as per the protocol, the physiotherapist in charge was observed and assessed by researchers of physiotherapy and clinical psychology background. The factors taken into assessment were appropriate exercise prescription for older persons with cognitively frailty, safety of the intervention delivery, manner of intervention delivery and adherence to the specified protocol. Fidelity of participants to the intervention was monitored by attendance logs of each participant for each intervention session. For the WE-RISE at Home, the number of completed session is self-reported by the participants over the biweekly phone calls with therapist as well as marked in the calendar within the activity manual. Additionally, elements of motivation, psychological and practical support, goal setting and focus on independence are incorporated as adherence measures older adults with frailty and cognitive impairment (64, 65).

#### Data Analysis

All statistical analyses will be carried out using the Statistical Package for Social Sciences (SPSS) software, version 23.0. An alpha level of (0.05) was considered for all the statistical tests used in the study. Two-sided *p* values of (0.05) and (80%) power will be statistically significant. Results of the randomized controlled trial will be analyzed using repeated measures analysis of variance for pre-test (Baseline Scores) and post-test (3rd month, 6^th^ month) for experimental and active control group. *Post-hoc* analysis will be conducted using Benferonni correction. Analysis will include nutritional assessment, cognitive frailty outcome measures, cognitive assessments, physical function assessments and quality of life.

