## Abstract

Following the rapid increase of the aging population, health promotion and prevention of physical disability and dementia in older persons are essential for healthy aging. For example, there may be a potential to prevent or reverse cognitive frailty, the co-existence of both physical frailty and cognitive impairment in older persons. However, evidence-based interventions targeting the prevention or potential reversibility of cognitive frailty among community dwelling older adults are scarce. In this paper, we described the rationale, development and delivery of a multi-domain intervention comprising multi-component physical exercise prescription, cognitive training, dietary counseling and promotion of psychosocial support, called the WE-RISE trial. The aim of WE-RISE intervention is to potentially reverse cognitive frailty. This is a two-armed, single blinded, randomized controlled trial conducted over a duration of 6 months, at senior citizen activity centers within the Klang Valley, Malaysia. Ambulating, community dwelling older adults aged 60 years and above with cognitive frailty are randomized into two groups; (1) intervention group: which receives an instructor based “WE-RISE” intervention for the first 3 months, and then a home-based “WE-RISE at Home” intervention for the following 3 months; (2) control group: usual care with no modifications to their daily routine. Primary outcome is cognitive frailty status and secondary outcome include physical function, cognitive performance, nutritional status, psychosocial status and quality of life which are obtained during baseline screening and subsequent follow ups at 3rd and 6th month. Description of the intervention is done using the template for intervention description and replication (TIDieR) checklist. This trial protocol has received approval from Research Ethics Committee of Universiti Kebangsaan Malaysia (UKM PPI/111/8/JEP-2018-558) and the Department of Social Welfare Malaysia (MyResearch Reference: JKMM 100/12/5/2: 2018/405). Trial registration number: ACTRN12619001055190.

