##### Primary outcome: cognitive frailty

This study operationalized cognitive frailty as proposed by Kelaiditi et al. (17) using Fried's criteria as outlined in the Cardiovascular Health Study to define physical frailty and the Clinical Dementia Rating Scale (CDR) to define objective cognitive impairment. The presence of one or two of the Fried's criteria was defined as pre-frailty, whilst the presence of three or more was defined as frail and a score of 0.5 on the CDR is defined as mild cognitive impairment (MCI) (17). Collectively, participants who had a combination of pre-frailty/frailty and MCI were categorized as cognitive frailty (Table 1).

**Table 1 T1:** Classification of cognitive frailty groups.

	**Criteria**	**Categorization**		
		**Robust**	**Cognitive pre-frailty**	**Cognitive frailty**
**Frailty** Fried et al. (6)	*Shrinking*: Unintentional weight loss of more than 5 kgs	0	1–2 Criteria	≥3 Criteria
	*Weakness*: Assessed with hand grip strength and adjusted for gender and body mass index against original cut-off points.			
	*Slowness*: Assessed with 5-meter gait speed test, adjusted for gender and height against original cut off points.			
	*Exhaustion*: Identified with two items from the CES-D scale.			
	*Low physical activity*: Identified by low scores of the PASE.			
**Cognitive impairment** Kelaiditi et al. (17)	Clinical Dementia Rating Scale score	0	0.5	0.5

*CES-D, Center for Epidemiologic Studies Depression Scale; PASE, Physical Activity Scale for Elderly*.

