##### Randomization

Participants with cognitive pre-frailty or cognitive frailty were randomized into intervention and control groups. Simple randomization was executed using the Research Randomizer computer program by the primary research coordinator (59). The trial flow is as illustrated in Figure 1. In this single blinded study, research assistants involved in data collection for the baseline and follow up outcome measures to prevent bias were blinded of the groups. Primary research coordinator was not involved in data collection. In order to minimize contamination between the intervention and control groups, an arrangement was made with the participating PAWEs to allow private and scheduled use of the facility on days that are not open for member activities.

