The WE-RISE intervention hopes to provide easier accessibility whilst enabling “age-friendly” health care delivery. If the intervention is found to be effective, the community-based nature of the intervention delivery may also be of lower cost as compared to the process of obtaining standard healthcare. Furthermore, it is not specific to the subset of older persons from lower socioeconomics but can also be applied amongst all walks of life and be practiced as a preventative strategy. The effectiveness and cost effectiveness of the WE-RISE intervention as compared to usual care on the reversal of cognitive frailty status among community dwelling older adults will be reported at the end of the trial. It is hoped that WE-RISE which is a multi-component and domain intervention will not only be beneficial in addressing cognitive frailty but also physical activity and general health in older persons.

In conclusion, we hope the address the need for a comprehensive and feasible intervention which is also sustainable in terms of delivery and cost for the well-being of older persons with cognitive frailty. The WE-RISE is versatile and can be administered within the community as well as a hospital or nursing home setting by most exercise instructors or primary healthcare practitioners with training.

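### The primary outcome is a category (cognitive frailty status) and the question is its reversal, but the only analysis named, repeated measures ANOVA on scores, does not fit it

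*Protocol article*

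**What the plan says.** The Abstract states: "Primary outcome is cognitive frailty status". The section on the primary outcome builds that status from two parts, the number of Fried criteria met (one or two is pre-frail, three or more is frail) and a CDR score of 0.5. It then merges the two frailty grades: "participants who had a combination of pre-frailty/frailty and MCI were categorized as cognitive frailty". Table 1, in the same section, keeps them apart in three columns: robust, cognitive pre-frailty and cognitive frailty.

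Everyone enrolled already has the condition in one grade or the other. The Randomization section says: "Participants with cognitive pre-frailty or cognitive frailty were randomized into intervention and control groups".

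The Discussion says the trial will report effectiveness against usual care "on the reversal of cognitive frailty status among community dwelling older adults".

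The Data Analysis section names a single method: "Results of the randomized controlled trial will be analyzed using repeated measures analysis of variance for pre-test (Baseline Scores) and post-test", with follow-up at months 3 and 6 and Bonferroni-corrected post-hoc tests. It lists the outcomes covered, and the cognitive frailty measures are among them. It names no other method, no definition of reversal and no primary visit.

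**The concern.** Repeated measures ANOVA compares mean scores over time. The primary outcome is a class, and the question is how many more participants leave that class under WE-RISE than under usual care. A method is stated for the primary outcome, and it is the wrong kind of method. That differs from a condensed article leaving a detail to its analysis plan.

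At stake is the trial's main conclusion. The named analysis delivers F tests over three visits. It specifies no difference in the proportion reversed, no odds ratio, and no visit to which the claim is tied. The choice of visit matters here: month 3 closes the supervised group phase and month 6 closes the home phase (section Intervention), so an effect could look different at each.

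**Working it through.** The article gives no sample size, reversal rate or effect size, so there is no figure of its own to reproduce. The check takes each reading of how ANOVA could be applied to the primary outcome.

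**Reading 1: two levels (the merged wording).** Code status 1 = cognitively frail, 0 = not. Eligibility makes every baseline value 1 in both arms, so the baseline variance is 0 and the baseline difference between arms is 0. Let d3 and d6 be the between-arm differences in the proportion reversed at months 3 and 6. In absolute size:

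- group main effect = (0 + d3 + d6)/3
- mean follow-up difference = (d3 + d6)/2
- ratio = (1/3)/(1/2) = 2/3, whatever the rates.

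For illustration, assume control reversal of 10% at both visits and intervention reversal of 20% then 30%. Then d3 = 0.10 and d6 = 0.20. The main effect is 0.30/3 = 0.10, the mean follow-up difference is 0.30/2 = 0.15, and the month 6 difference is 0.20. The group-by-time test is not diluted in this way: with a zero baseline difference it tests d3 = d6 = 0 jointly. It does not say which visit carries the claim.

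**Reading 2: three levels (Table 1).** Baseline now varies, because both grades are enrolled. Code robust = 0, pre-frail = 1, frail = 1 + k. Suppose the intervention moves an extra fraction a from frail to pre-frail and an extra fraction b from pre-frail to robust. The difference in means is −(k·a + b). The protocol fixes no k, so the weight of one kind of improvement against the other is arbitrary. If a and b have opposite signs, k can decide the sign of the result.

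Table 1 also does not cover every follow-up state. Crossing three Fried levels (0; 1–2; 3 or more) with CDR 0 and 0.5 gives 6 combinations, and the table classifies 3:

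| | CDR 0 | CDR 0.5 |
|---|---|---|
| 0 criteria | robust | unclassified |
| 1–2 criteria | unclassified | cognitive pre-frailty |
| 3 or more | unclassified | cognitive frailty |

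The unclassified cells are likely forms of partial improvement. A CDR above 0.5 has no column either.

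**Reading 3: component scores only** (grip strength, gait speed, CDR and so on). ANOVA is then usable, but the declared primary outcome and the reversal question go untested.

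**Power and type I error, under assumed inputs.** These are simulations with 3,000 runs per scenario, within-person correlation 0.6 and no missing data. They compare the Greenhouse–Geisser group-by-time test with a month 6 test of two proportions. The first three rows use coded 0/1 status, 62 per arm, with control reversal of 10% at both visits. The last three use a continuous score dichotomised at the eligibility cut, 100 per arm.

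| Assumed intervention effect | ANOVA | Month 6 proportions |
|---|---|---|
| 20% then 30% reversed | 0.73 | 0.81 |
| 30% at both visits | 0.84 | 0.81 |
| 30% then 20% | 0.71 | 0.35 |
| 0.35 SD at both visits | 0.87 | 0.61 |
| 0.2 then 0.4 SD | 0.86 | 0.73 |
| 0.4 then 0.2 SD | 0.86 | 0.24 |

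Under no effect, these tests rejected in 4.4% to 5.5% of runs. The direction of the power difference therefore depends on the assumed pattern and on what ANOVA is applied to.

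**The case against.** The strongest defence is that the Data Analysis section speaks of scores and of outcome measures in the plural. That can mean the Table 1 components, for which repeated measures ANOVA is conventional. The model for status, the primary visit and the effect measure would then be details left to a fuller document that is not shown. The component reading is possible, and nothing in the article says a coded status will be entered into ANOVA. But the section applies the method to the trial's results as a whole, expressly covers the cognitive frailty measures and offers nothing else. On the component reading, the primary outcome has no matching analysis.

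Four stronger claims are tempting, and the documents do not support them:

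- **That ANOVA costs power.** The article gives no sample size, rates or correlation. The advantage goes one way if the effect grows and the other if it is flat or fades. A fading effect is plausible once supervised sessions end.
- **That false positives are inflated.** The simulated error rates stay near 5%.
- **That ANOVA cannot estimate reversal at all.** With 0/1 coding, differences in visit means are risk differences, and the planned post-hoc tests may supply visit-level comparisons. The article does not state that coding, and the constant baseline would still break the model's variance assumptions.
- **That baseline never varies.** This holds only under the merged wording, not under the three columns of Table 1.

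**Conclusion.** The point holds as a mismatch between the primary outcome, the question and the named analysis. It rests on the article's own text and needs no assumed rates. Its one exact quantity is the two-thirds dilution of the group main effect, which applies under the merged two-level definition. Under three levels the defect is arbitrary spacing together with unclassified states. Under component scores the defect is that the primary outcome is untested. All three readings need the same correction, and it governs the trial's main conclusion. Nothing is concluded about power or type I error.

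**What to change.** 1. **Define reversal and fix one primary visit**, for example month 6, the end of the programme. Reconcile the merged wording with Table 1. State how these are classified: CDR 0 with one or more Fried criteria, CDR 0.5 with none, and a move from frail to pre-frail. State that worsening beyond CDR 0.5 counts as not reversed. Status requires a CDR of exactly 0.5, so a participant who deteriorates would otherwise leave the category and be scored a success.
2. **Make the primary analysis a between-arm comparison of the proportion reversed** at that visit, by logistic regression adjusted for baseline frailty category. Report the risk difference and odds ratio with 95% confidence intervals. Give the other visit as supportive, from a GEE or mixed logistic model with arm by visit. Adjustment for activity centre (PAWE) is optional: randomization was simple, and the number of centres is not given, so cells may be sparse.
3. **Keep ANOVA or other means-based methods** for the continuous secondary outcomes.

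The cost is a short rewrite of the outcome definition and the analysis paragraph, plus the decisions in step 1. SPSS, the software already named, has the procedures, and no new data or participants are needed. The downside is that a binary reversal analysis may have less power than one of continuous component scores, which can be kept as secondary.

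### Repeated measures ANOVA with baseline as a level of time leaves baseline unused for adjustment and by default needs all three visits; a baseline-adjusted mixed model is better for the continuous outcomes

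*Protocol article*

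**What the plan says.** The Abstract states that outcomes are "obtained during baseline screening and subsequent follow ups at 3rd and 6th month". The Data Analysis section then names one method for the trial results, "repeated measures analysis of variance for pre-test (Baseline Scores) and post-test" at months 3 and 6, and adds that post-hoc "analysis will be conducted using Benferonni correction". The software is "Statistical Package for Social Sciences (SPSS) software, version 23.0". The scope is broad: "Analysis will include nutritional assessment, cognitive frailty outcome measures, cognitive assessments, physical function assessments and quality of life".

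No baseline covariate and no mixed model are named. The article gives no sample size, SD, correlation between visits, drop-out rate or missing-data rule. These may stand in a fuller document, and their absence is not the point here. The point is the method that the article does name.

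**The concern.** Two consequences follow from the named method.

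**Baseline becomes an outcome.** With baseline as one of three time levels, the treatment effect is read from how the arms diverge from baseline. That amounts to comparing changes from baseline, or to a 2-degree-of-freedom arm-by-time test. In a randomised trial, adjusting the follow-up value for baseline estimates the same between-arm effect with smaller variance.

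**Incomplete participants drop out of the analysis.** Standard repeated measures ANOVA needs a value at every time level, so one missed visit removes the person. The comparison is then valid in general only if visits are missing completely at random. Participants here are pre-frail or frail with mild cognitive impairment. Only the intervention arm has two 90-minute centre sessions a week for 12 weeks, followed by 12 weeks of home sessions twice a week. Missed visits related to health or to arm are therefore plausible, and a complete-case comparison would no longer be protected by randomisation.

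**Working it through.** **Inputs from the article.** Visits at baseline, month 3 and month 6; two-sided alpha 0.05; two arms. The article mentions "80%) power will be statistically significant", but attaches no sample size, effect or SD to it, so that figure cannot be reproduced.

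**Assumed inputs.** n = 50 per arm, 1:1 allocation, effect 0.4 SD at both follow-ups, equal variances, compound symmetry with correlation ρ, and no missing data. Normal approximation for 1-df tests; noncentral F on 2 and 196 df for the interaction.

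**Formulas** (SD = 1; variance of an arm difference = (2/n) × V, with 2/n = 0.04):

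- Month 6, baseline-adjusted: V = 1 − ρ².
- Month 6, change from baseline: V = 2(1 − ρ).
- Arm-by-time test: noncentrality = (n/2) × Σ(d_t − mean d)² / (1 − ρ). With d = (0, 0.4, 0.4), the sum is 0.1067.
- Mean of both follow-ups, baseline-adjusted: V = (1 + ρ)/2 − ρ².
- Mean of both follow-ups minus baseline: V = 1.5(1 − ρ).

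**Example at ρ = 0.5.**

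- Adjusted month 6: 0.4/√(0.04 × 0.75) = 2.31, power 64%.
- Change to month 6: 0.4/√(0.04 × 1) = 2.00, power 52%.
- Arm-by-time: 25 × 0.1067/0.5 = 5.33, power 53%.

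| ρ | Month 6, adjusted | Month 6, change | Arm × time (2 df) | Mean of follow-ups, adjusted | Mean of follow-ups, change |
|---|---|---|---|---|---|
| 0.4 | 59% | 45% | 45% | 78% | 56% |
| 0.5 | 64% | 52% | 53% | 81% | 64% |
| 0.7 | 80% | 73% | 76% | 92% | 85% |
| 0.8 | 92% | 89% | 91% | 98% | 95% |
| 0.9 | >99% | >99% | >99% | >99% | >99% |

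**Removing the ceiling at high ρ.** The variance ratio of change to adjusted at month 6 is 2(1 − ρ)/(1 − ρ²) = 2/(1 + ρ). If the effect is instead set so that the adjusted analysis always has 80% power, the month-6 change contrast has 62%, 68%, 73%, 76% and 78% at ρ = 0.3, 0.5, 0.7, 0.8 and 0.9.

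**What missed visits add.** Suppose 20% drop out without returning, half before month 3 and half after. Complete-case change at month 6 then has 62%, 67%, 73%, 75% and 77% at the same correlations, almost unchanged. A complete-case analysis that does adjust for baseline keeps 78% to 80% at month 6, with drop-out up to 30%. So the handling of baseline accounts for nearly all of the loss. Deletion costs more power only when people miss month 3 and return: with 20% doing so, month-6 change has about 58% at ρ = 0.5 and 66% at ρ = 0.8.

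For scale, if a fraction m is missing independently at each follow-up, the share with an incomplete record is 1 − (1 − m)²: 10%, 19% and 28% for m = 5%, 10% and 15%. These rates are assumptions.

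**The case against.** The strongest reply is that, with complete data, the arm-by-time test is a valid randomised comparison, so much of this is a preference about efficiency on secondary outcomes. That stands. It limits the size of the point but does not remove it, because the more efficient analysis uses values already collected.

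A reader might also infer four stronger things, which the documents do not support.

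- *That power is much lower.* This is true at low correlation and not at high correlation, and the article gives no correlation. Setting the arm-by-time power against the adjusted mean of both follow-ups exaggerates the gap, because the two tests address different effects. The 2-df test draws on both follow-ups and can match or slightly exceed a single-visit adjusted test in some settings, such as ρ = 0.9. For the same 1-df effect, the adjusted analysis was never the weaker one.
- *That the article says incomplete participants are excluded.* It does not. Exclusion is the default behaviour of the method, and imputation could be specified elsewhere. The bias concern is conditional on that.
- *That the treatment test is the group main effect, diluted by a pre-treatment visit.* The article does not say which term is the treatment test, and arm-by-time is the usual choice in such a design.
- *That the Bonferroni tests are within-arm changes distorted by regression to the mean.* The article does not say which comparisons they cover. Selection used the frailty criteria and the dementia rating, so most of the continuous outcomes were not selection variables. Regression to the mean in both arms would not bias a between-arm test.

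**Conclusion.** The point holds in a limited form. The article commits to a method that leaves baseline unused for adjustment and that, unless missing data are handled elsewhere, rests on complete cases. For the same between-arm effect it has less power than a baseline-adjusted analysis. Under the stated assumptions the month-6 loss is about 14 percentage points at correlation 0.4 (59% against 45%), 11 to 12 at 0.5, 4 to 7 at 0.7, and small at 0.8 to 0.9. The direction for a like-for-like contrast follows from the variance formulas; the size rests on inputs that the article does not give.

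The argument about missed visits is mainly one of bias and needs no assumed sample size. It depends on whether missingness is related to health or arm, and on missing-data handling that is not shown. All of this concerns continuous outcomes only. Cognitive frailty status, the primary outcome, is categorical and is a separate matter under the same sentence.

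**What to change.** For each continuous outcome, replace the repeated measures ANOVA with a linear mixed model on the month-3 and month-6 values. Include the baseline value as covariate, arm, visit and arm-by-visit, with unstructured covariance. Include all observed follow-up data from everyone randomised, in the assigned arm. Such a model remains valid under the weaker assumption that missingness depends only on observed data.

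Report the between-arm difference with its 95% confidence interval at a prespecified visit, or averaged over both follow-ups. The article lists both visits without ranking them, so the investigators should state this choice before the data are seen. Base efficacy claims on between-arm contrasts, and say that the Bonferroni comparisons are of that kind. Specify a separate categorical model for cognitive frailty status.

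The cost is a change of analysis wording. The MIXED procedure in the SPSS software already named fits this model, and no further data are needed.
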